## 6.3 Discontinued subjects

The investigator may withdraw a subject from the study if he/she meets any of the following withdrawal criteria:

1. Any patients / patient's legally acceptable representative who wishes to withdraw his / her consent for participation in the study
2. The subject suffers from significant intercurrent illness or undergoes surgery during the course of the study.
3. Any patient who requires/uses an unacceptable concomitant medication as per the Protocol
4. Failure to take 80% of the study medication during the study period

|                                                                                  |                                                                                                       |                                                              |
|----------------------------------------------------------------------------------|-------------------------------------------------------------------------------------------------------|--------------------------------------------------------------|
| [figure not shown] | Clinical trial to evaluate efficacy and safety of Amla Extract (AMX160) in patients with Dyslipidemia | Project No. AN-03ASE
0115H2-SYN02
Ver.01, Dt: 01-01-15 |
|----------------------------------------------------------------------------------|-------------------------------------------------------------------------------------------------------|--------------------------------------------------------------|

5. If it is felt in Investigator's / Medical Expert's opinion that it is not in the patients' best interest to continue.

The date the subject is withdrawn from the study and the reason thereof will be documented in the CRF. Withdrawn subjects will be considered for modified intention to treat efficacy analysis, if they have completed at least 1 visit post randomization (visit 3; week 4) with laboratory evaluation. Though every effort will be made to adhere to the schedule of visits, a window period of  $\pm 5$  days will be permitted for all the visits

## 7 Study Assessments

All the subjects will undergo a thorough general physical examination including recording of vitals such as temperature, pulse, respiratory rate; systemic examination of cardiovascular, respiratory, central nervous systems and abdomen. The subjects will be evaluated as per the Inclusion & Exclusion Criteria. Haematological and biochemical laboratory investigations will be carried out as mentioned in section 7.3. If the patient is suffering from any other concomitant diseases and taking medications for the same, these details will also be recorded in the CRF.

### 7.1 Assessment of Efficacy

#### Lipid Parameters

Efficacy of the study medication will be assessed by serum lipid parameters including Triglycerides, Total Cholesterol, LDL and VLDL. All the lipid parameters will be measured after at least 8 hours of fasting.

#### Atherogenic index of Plasma

The atherogenic index of plasma (AIP) is defined as the base 10 logarithm of the ratio of the concentration of triglyceride (TG) to high density lipoprotein cholesterol (HDL-C), where each concentration is expressed in mmol/L.

$$AIP = \log_{10} \left( \frac{TG}{HDL-C} \right)$$

This quantity has been shown to reflect the distribution of particle sizes in lipoprotein subclasses and correlates significantly with the presence of risk factors for atherosclerosis such as gender, age, dyslipidemia and diabetes as well as positive findings on coronary angiography. Based on epidemiological data three risk categories for AIP have been suggested: low  $< 0.11$ , intermediate:  $0.11-0.21$  and high  $> 0.21$

|                                                                                  |                                                                                                       |                                                              |
|----------------------------------------------------------------------------------|-------------------------------------------------------------------------------------------------------|--------------------------------------------------------------|
| [figure not shown] | Clinical trial to evaluate efficacy and safety of Amla Extract (AMX160) in patients with Dyslipidemia | Project No. AN-03ASE
0115H2-SYN02
Ver.01, Dt: 01-01-15 |
|----------------------------------------------------------------------------------|-------------------------------------------------------------------------------------------------------|--------------------------------------------------------------|

### *Apo lipoprotein B (ApoB) and Apo lipoprotein A1 (ApoA1)*

Apo lipoproteins (apo) AI and B are structural proteins for high density lipoproteins (HDL-C), and the very low density-low density lipoprotein spectrum (VLDL-LDL) respectively. There is mounting evidence that implicates Apo lipoprotein B and Apo lipoprotein AI levels in the pathogenesis of CAD. This study will measure the levels of Apo lipoproteins (Apo) AI and B and their ratio (ApoA1/ApoB) during the course of the study.

### *FPG and HbA1c*

Amla extract is known to have an effect on blood glucose levels therefore, fasting plasma glucose and HbA1c will also be measured during the study. HbA1c will be measured by a method that is certified by the National Glycohemoglobin Standardization Program. For FPG, patient will be fasted, defined as no caloric intake for at least 8 hours.

### *Homocysteine levels*

High levels of plasma homocysteine are associated with increasing risk of damage to the arterial endothelium and thrombus formation.

### *Coenzyme Q10^15*

Coenzyme Q10 is an intracellular antioxidant that protects the membrane phospholipids, mitochondrial membrane protein, and LDLC from free radical-induced oxidative damage. It has been demonstrated that coenzyme Q10 has a cardio-protective impact on CAD. A higher level of plasma coenzyme Q10  $\geq 0.52 \mu\text{mol/L}$  is significantly associated with a reduced risk of CAD.

### *hs-CRP*

C-reactive protein (CRP) is a marker for inflammation and its increasing levels indicate an increased state of inflammation in the body. The levels are correlated with increasing risk of CAD. High Sensitivity-CRP levels Less than 1.0 mg/L are associated with 'Low' risk, 1.0-2.9 mg/L are associated with 'Intermediate' risk and levels Greater than 3.0 mg/L are associated with 'High' risk.

### *ATP goals*

Proportion of patients achieving all the three ATP goals i.e. Triglyceride < 150 mg/dL, LDL < 100 mg/dL, HDL > 40 will be calculated for the two groups.

|                                                                                  |                                                                                                       |                                                              |
|----------------------------------------------------------------------------------|-------------------------------------------------------------------------------------------------------|--------------------------------------------------------------|
| [figure not shown] | Clinical trial to evaluate efficacy and safety of Amla Extract (AMX160) in patients with Dyslipidemia | Project No. AN-03ASE
0115H2-SYN02
Ver.01, Dt: 01-01-15 |
|----------------------------------------------------------------------------------|-------------------------------------------------------------------------------------------------------|--------------------------------------------------------------|

### HMG Co-enzyme Reductase Activity

HMG-CoA reductase is the rate-controlling enzyme of the mevalonate pathway, the metabolic pathway that produces cholesterol and other isoprenoids. Medications affecting cholesterol synthesis inhibit the activity of this enzyme. The activity of HMG-CoA reductase will be measured in the two groups at baseline and end of the study using HMGR activity kit (----Details of Kit to be added----). This will help us understand the probable mechanism of action of Amla Extract in reducing lipid levels.

#### The primary efficacy endpoint would be:

1. Mean percent change in TG levels at the end of 12 weeks in the two groups

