After randomization, patients will be followed up on outpatient basis for period of 84 days (12 weeks) with scheduled visits on day 28, day 56 and day 84 post-randomization. Efficacy assessments will be carried out by laboratory investigations on each of the scheduled visits (except randomization visit). Clinical adverse events monitoring would be done on each visit and complete laboratory check-ups (both haematological and biochemical) and ECG will be repeated at the end of the study (12 weeks) so as to assess the safety of the study medication. Laboratory values obtained during the screening visit will be considered as baseline values for efficacy and safety analysis. Though every effort will be made to adhere to the schedule of visits, a window period of  $\pm 5$  days will be permitted for all the visits.

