### **6 Subject Eligibility**

#### **6.1 Inclusion Criteria**

- 1 Patients aged 30-65 years
- 2 Patients with dyslipidaemia having Triglycerides (TG) >200 mg/dL, LDL cholesterol > 130 mg/dL, Total cholesterol > 200 mg/dL and HDL cholesterol < 40 mg/dL for men and < 50mg/dL for women
- 3 Patients not taking any medication (including herbal product) for management of dyslipidaemia since last 4 weeks
- 4 Informed consent of the patient

|                                                                                  |                                                                                                       |                                                              |
|----------------------------------------------------------------------------------|-------------------------------------------------------------------------------------------------------|--------------------------------------------------------------|
| [figure not shown] | Clinical trial to evaluate efficacy and safety of Amla Extract (AMX160) in patients with Dyslipidemia | Project No. AN-03ASE
0115H2-SYN02
Ver.01, Dt: 01-01-15 |
|----------------------------------------------------------------------------------|-------------------------------------------------------------------------------------------------------|--------------------------------------------------------------|

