## 6.2 Exclusion Criteria

1. Patients with more than 2 of the following risk factors -
  - Cigarette smoking
  - Hypertension (BP >140/90 mmHg or on antihypertensive medication)
  - Family history of premature CHD (CHD in male first degree relative <55 years; CHD in female first degree relative <65 years)
  - Age (men >45 years; women >55 years)
2. Patients with uncontrolled cardiovascular disease or advanced atherosclerosis (e.g. history of stroke, myocardial infarction, life-threatening arrhythmia, or coronary revascularization within the preceding 6 months; unstable angina; congestive heart failure; known or suspected clinically significant valvular heart disease or uncontrolled hypertension (>160/100 mm of Hg or use of antihypertensive medications, dose of which is not stable in the last one month))
3. Patients with very high triglyceride levels i.e. > 500 mg/dL
4. Patients with FBS more than 150 mg/dL, using insulin, glitazones. Patients using other hypoglycaemics, dose of which is not stable in last one month
5. Pregnancy, lactation and female patients not using acceptable contraceptive measures (double barrier methods, oral or injectable hormonal contraceptives or surgical sterilization)
6. Patients with hepatic impairment (SGOT or SGPT levels > 3 Upper Limit of Normal (ULN)) or renal impairment (serum creatinine  $\geq$  2.0 mg/dl)
7. Patients with any other severe systemic illness and in the opinion of the investigator would be noncompliant with the visit schedule or study procedures
8. Patients with known history of hypersensitivity to amla or any product containing amla extract
9. Patients with continuing history of alcohol and / or drug abuse.
10. Patients with any other serious concurrent illness or malignancy.
11. Participation in another clinical trial in the past 3 months

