#### Visit 2: Randomization (Day 0)

- Inclusion & Exclusion Criteria re-check
- General physical and systemic examination
- Laboratory investigations - If patient satisfies all inclusion and exclusion criteria, other investigations i.e. Apo A1, Apo B, hs CRP, TSH, Homocysteine CoQ10, HbA1c and HMG Coenzyme Reductase activity will be done utilizing the same blood sample as collected at time of screening. No fresh blood sample will be collected on this visit
- Randomization and dispensing of study medication
- Recording of concomitant diseases and medications
- Instructions for lifestyle modification (healthy diet with aerobic exercise at least 4 days a week)

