#### 14.1 Sample size calculation

The sample size of 98 patients was calculated based on the following assumptions. Considering a mean reduction in TG between the group as 51 [29], the standard deviation as 76 [29] (effect Size 0.67 rounded to 0.7) with 5% alpha level (two sided) and power of 90%, at least 44 patients would be needed in each group. Assuming the dropout rate of 10% a total of 49 patients were enrolled in the study in each group. The enrolled patients would be assigned to either of the 2 treatment groups according to a centralized computer generated randomization plan in 1:1 ratio.

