### **14.4.3 Data Analysis**

The data collected from the CRFs will be analysed for demographics, efficacy & safety. Data will be presented as mean  $\pm$  SD/SE or number (percentage). Descriptive statistics will be used for different variables at baseline. *P* value of  $< 0.05$  will be considered as statistically significant. Standard statistical tests will be used to analyse the data obtained. For efficacy analysis both, modified Intention To Treat (mITT) analysis and Per Protocol (PP) analysis will be done. The PP analysis will be considered as definitive, while the mITT analysis will be considered as supportive during the trial analysis.

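### The primary endpoint is percent change in TG from one screening value that also decided entry, with no baseline adjustment named; adjusting the between-arm comparison for screening TG is a cheap gain in precision

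*Protocol*

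**What the plan says.** - **Endpoint.** Protocol section 7.1 gives the primary endpoint as "Mean percent change in TG levels at the end of 12 weeks in the two groups".
- **Baseline.** Section 4.3 states: "Laboratory values obtained during the screening visit will be considered as baseline values for efficacy and safety analysis". The laboratory schedule in section 7.3 shows TG at screening and weeks 4, 8 and 12, but not at Day 0. The Visit 2 description in section 8 confirms it: "No fresh blood sample will be collected on this visit".
- **Entry limits on the same value.** Section 6.1 admits "Patients with dyslipidaemia having Triglycerides (TG) >200 mg/dL", along with other lipid limits. Section 6.2 excludes "Patients with very high triglyceride levels i.e. > 500 mg/dL".
- **Analysis.** Section 14.4.3 says "Standard statistical tests will be used to analyse the data obtained". It names no model, covariate or transformation.
- **Comparison intended.** The objective in section 3 is efficacy relative to matching placebo, and section 14.1 sizes the trial on a difference between groups.

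**The concern.** The denominator of the primary outcome is one measurement, and patients entered only if that measurement was high enough. Its random error passes straight into percent change. TG is also expected to fall in both arms, because patients were selected on a high value and because all start lifestyle changes at randomization. A fall within an arm therefore says little about the extract; the contrast with placebo carries the information.

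Precision is at stake. Screening TG is already collected and is likely to predict week-12 TG. A comparison that ignores it leaves explainable variation in the error term and any chance imbalance in screening TG in the estimate. If TG is right-skewed, a few large values can also dominate an arithmetic mean of ratios.

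**Working it through.** **Plan's own figure.** Inputs from section 14.1: difference 51, SD 76 (no units; they read as mg/dL), effect size rounded to 0.7, two-sided 5%, 90% power.

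- Normal approximation: n = 2(1.960 + 1.282)² / 0.7² = 42.9, so 43 per group. The exact t calculation gives 44, as stated.
- Dropout: 44 / 0.9 = 48.9, so 49 per group and 98 in total.
- At the unrounded effect 51/76 = 0.671, power with 44 per group is 87.5% (exact t), so there is little precision to spare.

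**Analyses compared**, with B = screening TG and Y = week-12 TG:

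1. t-test on percent change, 100(Y − B)/B.
2. ANCOVA of Y on arm and B.
3. ANCOVA of log Y on arm and log B. The arm coefficient b converts to a percent difference, 100(e^b − 1).

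**Assumptions not in the documents.** Before selection, TG has mean 230 mg/dL and SD 70 or 90, with correlation r between screening and week 12. Entry is then cut to 200–500 mg/dL, with 44 per arm and 1,500 simulated trials per row. The Monte Carlo standard error of a power near 80% is √(0.8 × 0.2 / 1500) ≈ 1 point. All analyses in a row use the same simulated trials.

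| TG and effect | r | SD | Percent-change t-test | ANCOVA, raw TG | ANCOVA, log TG |
|---|---|---|---|---|---|
| Lognormal, 20% lower | 0.3 | 70 | 90.8% | 95.5% | 96.1% |
| | 0.3 | 90 | 72.5% | 77.4% | 80.9% |
| | 0.5 | 70 | 95.5% | 97.1% | 97.2% |
| | 0.5 | 90 | 84.4% | 87.5% | 89.0% |
| | 0.7 | 70 | 99.5% | 99.6% | 99.7% |
| | 0.7 | 90 | 95.3% | 96.3% | 97.3% |
| Normal, 51 mg/dL lower | 0.3 | 70 | 90.4% | 93.7% | 92.5% |
| | 0.3 | 90 | 76.5% | 80.7% | 77.1% |
| | 0.5 | 70 | 95.9% | 96.7% | 95.5% |
| | 0.5 | 90 | 82.7% | 84.3% | 80.3% |
| | 0.7 | 70 | 99.7% | 99.7% | 99.5% |
| | 0.7 | 90 | 95.6% | 96.2% | 94.7% |

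**Reading the table.**

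- ANCOVA on raw TG gains 0 to 4.9 points (72.5% to 77.4%) and never loses.
- With lognormal TG, log-ANCOVA gains 0.2 to 8.4 points (72.5% to 80.9%).
- With normal TG and an additive effect, log-ANCOVA lies between +2.1 points (90.4% to 92.5%) and −2.4 points (82.7% to 80.3%).

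**Wider lognormal runs** (log SD 0.30 to 0.50, 20% reduction). The largest gain of log-ANCOVA over the percent-change t-test was about 10 points, from 66% to 76% at r = 0.3. At r = 0.5, power rose from 79% to 85%.

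**In patients.** Log-ANCOVA needs 77% to 95% of the number that the percent-change t-test needs when TG is lognormal (r from 0.3 to 0.85), and 97% to 108% when TG is normal with an additive effect.

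**Keeping percent change as the outcome and adding screening TG as a covariate** also helps. For r = 0.3, 0.5 and 0.7, power goes from 67%, 79% and 93% to 72%, 82% and 94% (lognormal, 20% reduction). With a normal, additive effect of 45 mg/dL, it goes from 76%, 85% and 96% to 81%, 88% and 97%.

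**Type I error**, checked in one lognormal scenario (log SD 0.4, r = 0.5): about 5% for both the percent-change t-test and log-ANCOVA.

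**The case against.** The strongest reply is that the protocol fixes an endpoint and not a model. Section 14.4.3 neither prescribes an unadjusted test nor rules out a covariate or a log scale. An ANCOVA of percent change on screening TG would satisfy section 7.1 as written, and such choices are often left to a statistical analysis plan, which is not at hand. This stands: that the analysis would be unadjusted is an inference, and the absence of a model is not itself an error. The point is that the one summary the protocol does fix, an arithmetic mean percent change, can be improved. A later plan could not replace that summary with a geometric-mean ratio without departing from section 7.1.

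Two stronger readings are tempting, and the documents support neither.

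- **Bias.** A reader might infer that selecting on the screening value biases the primary comparison, or that only an adjusted difference answers the objective. Under 1:1 randomization, regression to the mean and lifestyle advice affect both arms alike in expectation. The unadjusted between-arm difference is valid, and its standard error already reflects chance imbalance. The endpoint speaks of change in each group, but sections 3 and 14.1 make clear that a comparison with placebo is intended.
- **A large saving.** A reader might apply the textbook variance ratio of ANCOVA to a change score, (1 + r)/2, and expect 20% to 30% less variance at r = 0.6 to 0.4. That ratio requires equal variances at both times. Restricting entry to 200–500 mg/dL shrinks the spread at screening but not correspondingly at week 12. With lognormal TG under that restriction (median 180 to 280, log SD 0.3 to 0.5, r 0.4 to 0.6 before selection), the ratio is 0.81 to 0.95, a saving of 5% to 19%. A simple change score is also not the protocol's endpoint.

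**Conclusion.** The concern holds as a cheap improvement. It is not an error that threatens the trial's validity. Adjusting for screening TG is worth roughly 0 to 10 power points over a t-test on percent change at 44 per arm. The gain is largest at a low baseline-to-week-12 correlation and almost disappears at 0.7 or above.

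The gain from adjustment itself appears under both distributions tried, provided the scale suits the data. The added gain from logs appears only when TG is right-skewed; with normal TG and an additive effect it is about nil and can be a small loss. All these sizes rest on assumed distributions and correlations, because the protocol gives neither.

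**What to change.** In sections 7.1 and 14.4.3:

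- State that the primary result is the between-arm difference in TG at week 12 versus placebo, adjusted for screening TG by ANCOVA. Log TG is preferred, with the estimate back-transformed to a percent difference and given a 95% CI.
- Apply the same baseline adjustment to the other continuous endpoints.
- Present percent change within each arm descriptively only.

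**Cost.** No extra patients, visits or samples. The change is not wholly free: on the log scale the estimand moves from a difference in arithmetic mean percent changes to a ratio of geometric means. The primary endpoint must therefore be reworded, and section 14.1 should say how "Considering a mean reduction in TG between the group as 51" and "the standard deviation as 76", which are not log-scale figures, relate to it. If the sponsor prefers to keep percent change as the outcome, naming screening TG as a covariate secures part of the gain without altering the endpoint. The choice should be fixed before unblinding.

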#### The secondary efficacy endpoint would be:

1. Mean percent change in Total cholesterol, LDL and VLDL levels at the end of 12 weeks in the two groups
2. Mean change in the Atherogenic Index of Plasma (Log (TG/HDL))
3. Mean change in apolipoprotein B (apoB), apolipoprotein A1 (apoA1) and their ratio at the end of 12 weeks in the two groups
4. Mean change in FPG and HbA1c levels at the end of 12 weeks in the two groups
5. Mean change in hs-CRP, homocysteine, Coenzyme Q10 levels at the end of 12 weeks in the two groups
6. Proportion of patients achieving ATP goals (Triglyceride < 150 mg/dL, LDL < 100 mg/dL, HDL > 40) at the end of the study
7. Change in the HMG-CoA reductase activity at the end of the study in the two groups

## **7.2 Assessment of Safety**

The safety of the study medication will be assessed by recording the adverse events occurring during the entire course of the study, as mentioned in detail in “Adverse Events” section of the protocol. All observed (during general and physical examination of patients or in the laboratory parameters) or volunteered adverse events regardless of suspected causal relationship to the study test product will be recorded on the adverse event page of the CRF. ECG of all the patients will be done at the screening and at the end of the study.

|                                                                                  |                                                                                                       |                                                              |
|----------------------------------------------------------------------------------|-------------------------------------------------------------------------------------------------------|--------------------------------------------------------------|
| [figure not shown] | Clinical trial to evaluate efficacy and safety of Amla Extract (AMX160) in patients with Dyslipidemia | Project No. AN-03ASE
0115H2-SYN02
Ver.01, Dt: 01-01-15 |
|----------------------------------------------------------------------------------|-------------------------------------------------------------------------------------------------------|--------------------------------------------------------------|

